## Abstract

**Background:**

Falls in hospitals are common, resulting in injury and anxiety to patients, and large costs to NHS organisations. More than half of all in-patient falls in elderly people in acute care settings occur at the bedside, during transfers or whilst getting up to go to the toilet. In the majority of cases these falls are unwitnessed. There is insufficient evidence underpinning the effectiveness of interventions to guide clinical staff regarding the reduction of falls in the elderly inpatient. New patient monitoring technologies have the potential to offer advances in falls prevention. Bedside sensor equipment can alert staff, not in the immediate vicinity, to a potential problem and avert a fall. However no studies utilizing this assistive technology have demonstrated a significant reduction in falls rates in a randomised controlled trial setting.

**Methods/Design:**

The research design is an individual patient randomised controlled trial of bedside chair and bed pressure sensors, incorporating a radio-paging alerting mode to alert staff to patients rising from their bed or chair, across five acute elderly care wards in Nottingham University Hospitals NHS Trust. Participants will be randomised to bedside chair and bed sensors or to usual care (without the use of sensors). The primary outcome is the number of bedside in-patient falls.

**Discussion:**

The REFINE study is the first randomised controlled trial of bedside pressure sensors in elderly inpatients in an acute NHS Trust. We will assess whether falls can be successfully and cost effectively reduced using this technology, and report on its acceptability to both patients and staff.

**Trial Registration:**

**ISRCTN trial number**: ISRCTN44972300.

## Background

Falls in hospitals are common, ranging from 3 to 14 for every 1,000 bed days [1]. Over 200,000 falls were reported to the National Patient Safety Agency's (NPSA) National Reporting and Learning System (NRLS) in the 12 months from September 2005 to August 2006, with falls data being reported from 98% of organisations providing in-patient services [2]. In-patient falls result in injury and anxiety to patients and large costs to NHS organisations, including the costs of treating injuries, increased hospital stay, complaints and litigation [3-5].

Elderly in-patients are at particular risk of falling with the incidence of falls being almost triple that for community-dwelling older people [6]. Several factors contribute to this including; age, a history of falling, impaired mobility and special toileting needs. People with dementia are more likely than those without it to require hospital admission, and are at least twice as likely to fall [7-9]. Up to 30% of in-patient falls occur during the first 48 hours of the patients' admission and 75% of in-patient falls occur in the first two weeks of hospital stay [7,10,11].

Our hospital audit data are consistent with published data [2] and has shown that more than half (53%) of all in-patient falls in elderly people in acute care settings occurred at the bedside, during transfers or whilst getting up to go to the toilet. In the majority of cases these falls were unwitnessed. Where patients had been advised to call for assistance they were often reluctant to ask for help as they "did "not want to bother the nurses" or were unable to do so because of cognitive impairment.

Prevention of falls is a priority for NHS policy makers and practitioners. The Healthcare Commission has used falls prevention as a focus for inspecting compliance under patient safety [12]. Despite our increasing knowledge of the aetiology and epidemiology of falls, there is a dearth of evidence for effective falls prevention in hospitals [13-15]. There is good evidence for falls prevention in the community dwelling elderly [16-18], but these findings are unlikely to generalise to the acute hospital setting.

Advances in telecare afford innovative approaches to the reduction of falls. Assistive technology such as bed and bedside chair alarms, which alert nearby staff that a person is attempting to leave the bed or chair, are increasingly being used in the NHS [19]. However there is a lack of evidence underpinning the use of such systems. Of the few studies that have been published, none have demonstrated a significant reduction in falls rates in a randomised controlled trial setting [20,21].

The current study will address shortcomings in the evidence base. We will assess whether falls can be successfully and cost effectively reduced using pressure sensor-pager technology in a randomised controlled trial.

## Objectives

### Main research hypothesis

The hypothesis to be tested is that the use of a pressure sensor alert system, incorporating a radio-paging alerting mode to alert staff to patients rising from their bed or chair, can decrease the number of bedside falls, in older people hospitalized in an acute care setting.

### Secondary research hypotheses

1. There is a beneficial effect of pressure sensors upon health outcomes (transfer and mobility, fear of falling, quality of life, length of hospital stay and residential status on discharge) in hospitalised older people.

2. That the intervention above is cost-effective compared to usual care from a secondary care NHS perspective.

3. That there are groups of patients in whom the health or economic benefits from the intervention are greatest.

4. That the sensor system is acceptable to staff and patients and practical for use in an acute hospital setting.

## Methods/Design

The study is a pragmatic parallel-arm randomised controlled trial. Subjects are randomised either to receive bed and chair sensor equipment, or standard care (control arm), see Figure 1 (Flow of participants through the study).

**Figure 1 F1:**
[figure not shown]
**Flow of participants through the study**.

### Setting

Five acute older persons' care wards at Nottingham University Hospitals NHS Trust (NUH).

### Participants

All patients admitted to five older persons' care wards are eligible for inclusion into the trial. Patients will be excluded from the study if they were permanently bed bound prior to admission, moribund/unconscious, or receiving end of life care on admission, or if they have previously been included in the study in an earlier admission.

### Ethics and consent

The study is executed in accordance with the principles laid down in the Helsinki Declaration [22]. This study was approved by Nottingham Research Ethics Committee 1 on the 23rd May 2008 (Reference: 07HC006; MREC: 08/H0403/40).

Written, informed consent is obtained, in accordance with International Conference on Harmonisation Guidelines for Good Clinical Practice (ICH GCP) [23]. In patients who are confused (dementia/delirium such that the subject cannot understand the nature of consenting to a research study and the study process), consent is obtained by carers or other proxies including staff, following the established framework of Berghmans, used in previous ethically approved studies in older persons with dementia [24].

### Intervention

Those participants randomised to the intervention arm of the trial will receive bedside chair and bed pressure sensors for the duration of their ward admission.

Each sensor device consists of a flexible pressure pad enveloped in thin foam encased in a durable plastic coating such that it confirms to hospital infection control policies. The bed sensor (760 mm × 250 mm × 3 mm) is placed between the bed mattress and the base of the bed in a horizontal position directly under the hip region. The chair sensor (360 mm × 175 mm × 3 mm) is positioned on top of the chair base and/or under a cushion.

The sensors detect pressure changes as the patient rises from the bed or chair, whereafter an alert is sent via radio page to a handheld pager carried by nursing staff. The pager provides the location of the call so staff can respond rapidly and ensure the patient is safe. In this way the sensor system provides an early warning to staff that the patient has left the bed or chair, and may therefore avert a potential fall.

Sensor units are leased from Tunstall Ltd. and are CE marked, complying with the regulatory authorities. Nursing staff on participating will be trained to use the sensors prior to trial recruitment. Members of the research team fit the sensors to the beds and chairs with the sensors left in place until the participant is discharged.

### Sample size

Based on data obtained from our wards during 2005, we anticipate a rate of bedside falls of 8.0 per 1,000 bed days in the control group, assuming that 53% of all falls occur at the bedside and that the average length of stay is 19 days (mean number of falls per patient = 0.15). To detect a 35% reduction in the rate of bedside falls among the intervention group, assuming 80% power, alpha = 0.05 and an over dispersion parameter of 1.5 (to allow for non-independence of falls within individuals), 905 participants are required in each arm of the trial.

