### Outcome measures

#### Definition of primary and secondary outcome measures

The primary outcome measure is the number of bedside in-patient falls per 1,000 bed days from time of randomisation until the participant is discharged from the ward.

A bedside fall is defined as an unexpected event in which the participant comes to rest on the ground, floor or lower level in the area around the bedside, with the bedside being defined as the area encompassed by the curtained area surrounding the bed. For participants in side rooms, the bedside is defined as the area of the room.

The secondary outcome measures are:

a. Number of injurious in-patient falls per 1,000 bed days, defined as falls resulting in abrasion, bruise, swelling, cut, laceration, dislocation, fracture or muscle sprain or strain.

b. Length of hospital stay.

c. Residential status on discharge.

d. Transfer/mobility score and activities of daily living, measured using the Barthel Index [26].

e. Fear of falling, measured using the Modified Falls Efficacy Scale (mFES) [27] to ascertain any differential fear of falling in the two participant groups due to an increased awareness of a potential for a fall, or a greater sense of safety arising from sensor use.

f. Health related quality of life, measured using the EUROQOL EQ-5D [28].

g. Participant and staff experience of using bed and chair sensors. This sub-study will be reported separately.

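### The inputs to the planning mean of 0.15 bedside falls per patient do not match the primary outcome's place or time window, so the stated 80% power is likely too high

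*Protocol article*

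**What the plan says.** In the protocol article, Sample size: "we anticipate a rate of bedside falls of 8.0 per 1,000 bed days in the control group", based on data from the trial wards in 2005 and "assuming that 53% of all falls occur at the bedside and that the average length of stay is 19 days", which leads to "mean number of falls per patient = 0.15". The target is a bedside fall rate 35% lower with sensors, "assuming 80% power, alpha = 0.05 and an over dispersion parameter of 1.5", and the result is 905 per arm.

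Background: the hospital's audit found that 53% of in-patient falls in elderly people "occurred at the bedside, during transfers or whilst getting up to go to the toilet". The Abstract describes the same three-part group. The Background also says: "Up to 30% of in-patient falls occur during the first 48 hours" of admission.

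Definition of primary and secondary outcome measures: the outcome is bedside falls per 1,000 bed days from randomisation until discharge from the ward, with "the bedside being defined as the area encompassed by the curtained area surrounding the bed". For side rooms, the whole room counts.

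Randomisation follows written or proxy consent (Ethics and consent), and time since admission is a baseline item (Baseline data). Some of the stay therefore comes before the outcome window opens.

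**The concern.** Power for a comparison of fall rates depends on the expected number of falls. Two inputs to that number describe something other than the outcome.

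- **Place.** The audit group is defined partly by activity (transfers, getting up for the toilet), while the outcome is defined only by location. A fall during a transfer or toilet trip beyond the curtains belongs to the 53% but is not a primary outcome event.
- **Window.** The rate is multiplied by an average stay of 19 days, but falls count only from randomisation. By the protocol's own account falls are concentrated early, so the days lost may carry more than their share of falls.

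Taken alone, each mismatch lowers the expected events. No allowance for lost events is stated, and 905 reproduces without one. If the trial shows no effect, readers will rely on the stated power to judge which reduction it could have excluded.

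**Working it through.** **Inputs (Sample size).** Control rate 8.0 per 1,000 bed days; stay 19 days; rate ratio 1 − 0.35 = 0.65; overdispersion 1.5; alpha 0.05; power 80%; 905 per arm. Allocation is equal (Randomisation). Sidedness is not stated, so two-sided is assumed.

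**Step 1: the planning mean.** 8.0 × 19 / 1,000 = 0.152, which agrees with the stated 0.15. The multiplication is correct; the question is what the inputs measure.

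**Step 2: the plan's own sample size.** The Signorini formula for Poisson regression with a binary covariate, multiplied by the overdispersion φ, is

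n per arm = φ × [z(0.975) × √4 + z(0.80) × √(2 + 2/0.65)]² / (2 × μ × (ln 0.65)²).

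The bracket is 1.960 × 2 + 0.842 × 2.253 = 5.816, and its square is 33.83. Also (ln 0.65)² = 0.1856.

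- μ = 0.152: 1.5 × 33.83 / (2 × 0.152 × 0.1856) ≈ 900 per arm.
- μ = 0.15: ≈ 912 per arm.

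The stated 905 lies between them, so it follows from the plan's inputs.

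**Step 3: power at 905 per arm for other means.** The same formula turned round is

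power = Φ{[|ln 0.65| × √(2 × 905 × μ / 1.5) − 1.960 × 2] / 2.253}.

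At μ = 0.152 this is Φ[(0.4308 × 13.543 − 3.920) / 2.253] = Φ(0.85) = 80%. Expected events over both arms are 905 × μ × 1.65.

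| Scenario | Mean μ | Events | Power |
|---|---|---|---|
| As planned | 0.152 | 227 | 80% |
| 1 day lost, constant rate (8.0 × 18 / 1,000) | 0.144 | 215 | 78% |
| 2 days lost, constant rate (8.0 × 17 / 1,000) | 0.136 | 203 | 76% |
| 20% of the 53% outside the curtains (0.8 × 0.152) | 0.122 | 182 | 72% |
| All 30% of early falls lost, stays over 48 h only (0.106 / 0.90) | 0.118 | 176 | 71% |
| All 30% of early falls lost, fixed 19-day stay (0.7 × 0.152) | 0.106 | 159 | 67% |
| 20% outside and 30% lost (0.8 × 0.106) | 0.085 | 127 | 58% |

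The 0.118 row assumes exponential stays with a mean of 19 days and randomisation at 48 hours. A share exp(−2/19) = 0.90 then stays long enough to be enrolled, and the remaining falls are spread over those patients only.

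**What is assumed.** The documents give neither the share of the 53% inside the curtained area nor the delay from admission to randomisation. The 20% is purely illustrative. The 30% rows are an upper bound: the Background says up to 30%, citing published work, and the rows need every early fall to precede randomisation.

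**The case against.** The strongest reply is that the stated calculation is not wrong. The mean multiplies out, and 905 reproduces at about 80% power. The Sample size section labels 8.0 as a rate of bedside falls on these wards. Transfers and getting up can take place inside the curtains, and the side-room rule widens the outcome, so the excess in the 53% may be small. The 19 days may already be ward stay, since the sentence refers to the wards' own data; the clear mismatch is then only at the start of the window. Some effects run the other way. Permanently bed-bound, moribund or unconscious, and end-of-life patients are excluded, which could raise the rate above that of 2005. Patients with very short stays may be missed before consent, which would lengthen average follow-up.

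All of this stands, and it limits the point to a likely direction of unknown size. It does not remove the mismatch. The Background and the Sample size section give the same 53% two different meanings, and a stay is used where the outcome runs from randomisation.

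Three stronger readings are tempting and not supported:

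- **An arithmetic or formula error.** A simple Wald calculation on the log rate ratio gives about 74% power at 905 per arm. The plan's figure reproduces under another recognised formula, so that gap cannot be charged to these inputs.
- **A conflict with the published range.** 8.0 / 0.53 = 15.1 total falls per 1,000 bed days, above the 3 to 14 in the Background. That range is for hospitals in general, and the Background says elderly in-patients are at particular risk. A higher rate on acute elderly wards is no contradiction.
- **Demonstrated loss of power.** With the shares and delays not given and offsetting effects not quantified, the documents do not show that power is below 80%.

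**Conclusion.** The point holds as a mismatch between planning inputs and outcome. Expected events and the stated 80% power are likely too high, but this is not demonstrated. If only a day or two is lost at a constant rate and most of the 53% lies inside the curtains, the loss is 2 to 4 percentage points. A fifth of the 53% outside the curtains would cost about 8 points. Losing all the early falls would bring power to 67% to 71%, and both together at the extreme to 58%. These figures rest on the formula that reproduces 905, a two-sided 5% test, a ratio of 0.65, dispersion of 1.5, and assumed shares and delays that the documents do not supply.

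**What to change.** 1. Re-tabulate the planning rate under the outcome definition (curtained area, or whole side room). The trial already plans to collect falls data from incident forms for the 12 months before it starts, and the forms record place (Follow-up data).
2. Replace the 19-day stay with the expected days from randomisation to ward discharge. Time since admission is recorded at baseline and length of stay at discharge, so the delay can be estimated from pooled data without looking at outcomes by arm. Until then, state an assumed range.
3. Restate expected bedside falls per participant, and the power or detectable reduction for 905 per arm, as a range in a revised Sample size paragraph. Say what the 53% covers, so that the Background and Sample size sections agree.

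No extra enrolment is proposed. The cost is a few hours on data already being collected, and a stated power that is likely to look less favourable.

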### Analysis

#### Quantitative analysis

Analyses will be undertaken on an intention to treat. Intention to treat analysis is defined in this study as an a priori plan to analyse the data according to the groups to which the subjects were randomised regardless of the treatment they received.

Fall rates for each group will be expressed as number of bedside falls per 1,000 bed days. The number of bedside falls per patient will be compared between groups using Poisson regression allowing for over dispersion, with length of stay in days as an offset. Crude models containing intervention group only will be fitted initially, whilst additional models will adjust for the effects of age, MMSE and mobility/transfer scores. Interactions between each of these three variables and treatment group with respect to our primary and secondary outcome measures will also be examined, with covariates dichotomised where necessary. For other secondary outcome measures, groups will be compared using the independent samples t-test for continuous outcomes (or Mann-Whitney U test if assumptions for using the t-test are not satisfied following appropriate transformations of the data) and the chi-square test for binary/categorical outcomes. The rate of falls in the trial wards in the 12 months prior to the trial commencing will be compared with the rate of falls in the control arm during the trial using Poisson regression, allowing for overdispersion as appropriate. A significance level of p < 0.05 will be used for all analyses.

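### On the plan's own inputs, 905 per arm gives the planned over-dispersed Poisson comparison about 73–75% power (about 77% at best), not the stated 80%

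*Protocol article*

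**What the plan says.** The Sample size section of the protocol article starts from 2005 ward data: "we anticipate a rate of bedside falls of 8.0 per 1,000 bed days in the control group". It assumes that "the average length of stay is 19 days" and prints the result as "mean number of falls per patient = 0.15". The target is stated as "To detect a 35% reduction in the rate of bedside falls among the intervention group", and the remaining inputs as "assuming 80% power, alpha = 0.05 and an over dispersion parameter of 1.5". The conclusion is that "905 participants are required in each arm of the trial".

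The section names no formula. It does not say whether alpha is one- or two-sided, or whether 1.5 multiplies the variance or is some other dispersion parameter. It explains 1.5 only as an allowance for repeated falls in the same person.

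The Quantitative analysis section compares bedside falls per patient "using Poisson regression allowing for over dispersion", with length of stay as offset. On significance it says: "A significance level of p < 0.05 will be used for all analyses".

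**The concern.** All the inputs are printed, so the power claim can be checked against the planned test. In that test the standard error of the log rate ratio comes from the falls observed in both arms, scaled by the estimated dispersion. If sensors work as hoped, the sensor arm contributes fewer falls and the comparison is less precise than one in which both arms fall at the control rate. A sample size that leaves this out, or that uses a variance smaller than the Poisson variance, will promise more power than the analysis has.

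This is the article's only power statement. If it is too high, the chance of missing a true 35% reduction is understated, and a non-significant result may be taken as stronger evidence against sensors than it is.

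**Working it through.** **Inputs** (Sample size section unless stated)
- Control mean per patient: m1 = 0.15 as printed; 8.0/1,000 × 19 = 0.152 unrounded.
- Sensor mean: m2 = 0.65 × m1 = 0.0975 or 0.0988.
- |ln 0.65| = 0.4308.
- Dispersion φ = 1.5, read as variance/mean (assumption).
- Alpha 0.05, two-sided (assumption): z = 1.960. Power 80%: z = 0.8416. (1.960 + 0.8416)² = 7.849.
- Equal allocation (Randomisation section).

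**Step 1: where 905 could come from**

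(a) Poisson-regression formula with the control rate in both arms under the null:

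n = φ × [1.960 × √(2/m1) + 0.8416 × √(1/m1 + 1/m2)]² / 0.4308²

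This gives 911.5 at m1 = 0.15 and 899.5 at m1 = 0.152. It gives 905.4 at 0.151, a value that the article does not print.

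(b) The two means treated as proportions, with the result multiplied by 1.5. With unpooled variance and 0.152 against 0.0988:

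n = 1.5 × 7.849 × (0.152 × 0.848 + 0.0988 × 0.9012) / 0.0532² = 906.6

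With pooled variance under the null, the result is 912 (0.152) to 926 (0.15).

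Both routes lie close to 905, and nothing in the article chooses between them.

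**Step 2: power of the planned comparison at 905 per arm**

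Log rate ratio, m1 = 0.152:
- SE = √[1.5/905 × (1/0.152 + 1/0.0988)] = 0.1664
- 0.4308 / 0.1664 = 2.589
- Power = Φ(2.589 − 1.960) = 73.5%

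| Method | m1 = 0.15 | m1 = 0.152 |
|---|---|---|
| Log rate ratio | 73.0% | 73.5% |
| Difference of means | 73.6% | 74.2% |
| Square-root scale | 74.1% | 74.7% |
| Log rate ratio, null variance at the average rate | 74.4% | 75.0% |

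Simulations of the quasi-Poisson Wald test, with counts of variance 1.5 × mean in both arms, gave 73.8% to 74.7%, and 74.8% with variable length of stay. Rejection under the null was about 5%. Rounding of the mean (0.145 to 0.155) moves the formula results only to about 72–76%.

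If patient heterogeneity is the same in both arms, the variance/mean ratio is 1.5 in controls and 1 + 0.5 × 0.65 = 1.325 in the sensor arm. Simulated power is then about 77%.

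**Step 3: size needed for 80%, common dispersion**

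Log rate ratio: n = 7.849 × 1.5 × (1/m1 + 1/m2) / 0.4308² = 1,060 (m1 = 0.152) or 1,074 (m1 = 0.15). Difference of means, m1 = 0.152: 1,043. Null variance at the average rate: 1,027 to 1,040. The range is about 1,030 to 1,075 per arm.

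**Step 4: reduction detectable with 80% power at 905**

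Solving the log-rate-ratio formula at m1 = 0.152 gives a 37.6% reduction.

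**Step 5: why both routes fall short**
- Route (a) takes the null variance from 2 × 905 × 0.152 = 275 falls. The design alternative yields 905 × (0.152 + 0.0988) = 227.
- Route (b) uses p(1 − p), which is smaller than the Poisson variance p of the planned count model.

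**The case against.** Four points deserve weight.

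1. *905 is not shown to be an arithmetic slip.* Route (a) is a published method with nominal power of 79.7% to 80.2% at 905. This stands. A reader might infer that the sponsor miscalculated, or that 905 can only have come from assuming the control rate in both arms. The documents support neither: no formula is named, the exact match under (a) needs an unprinted mean of 0.151, and (b) fits about as well. The point concerns the power of the planned test, not the origin of 905.

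2. *The shortfall depends on how 1.5 is read.* As a negative binomial dispersion (variance = m + 1.5m²), 905 would give about 83% power. But 80% would then need only about 833 to 843 per arm, so this reading does not lead to 905, and it fits a Poisson model with over-dispersion less well.

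3. *Alpha might be one-sided.* Power at 905 would then be about 82–83%. But 80% would need only about 835 to 846 per arm, so this does not explain 905 either.

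4. *Dispersion may fall with the mean.* This is plausible, because the article ties 1.5 to falls clustering within individuals. It stands, and it cuts the shortfall to about 3 points without removing it.

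It is also fair that the confidence interval from the final regression will show the precision achieved, whatever power was claimed.

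**Conclusion.** The stated 80% does not hold for the planned analysis under any reading examined that leads to 905. With two-sided alpha and a common variance/mean ratio of 1.5, power is about 73–75%, which is 5 to 7 points short. The risk of missing a true 35% reduction is about 26% instead of 20%. If dispersion is lower in the sensor arm, power is about 77% and that risk about 23%. The two-sided alpha and the meaning of 1.5 are assumptions, because the article states neither.

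A reader might infer that the trial must be enlarged. That does not follow. The detectable reduction moves only from 35% to about 38%, and the planned test and estimate are unaffected. What is wrong is the power attached to 905.

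**What to change.** Keep 905 per arm. In the Sample size section, name the formula used, state whether alpha is two-sided, and define the over-dispersion parameter. If 1.5 is the variance/mean ratio, restate the claim as about 74% power for a 35% reduction, or 80% power for a reduction of about 38%. If it means something else, give the matching calculation and the power at 905 that follows from it.

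This changes wording only. It needs no more participants and alters no analysis; the only downside is a slightly less favourable stated power.
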